#### Secondary outcomes

The secondary outcomes include embryology data, other pregnancy outcomes, and the scale and questionnaire measurement. The schedule of measurements and visits for each outcome are shown in **Table 4**. We will also observe the patient retention rate and treatment adherence. Retention rate is defined as the percentage of patients enrolled at baseline and who completed all follow-up measurements. Treatment adherence is assessed using attendance at the treatment sessions. Successful pilot targets are defined as the recruitment of 114 participants over 4 months, an 80% retention rate (25), and at least four treatment sessions attended.

Embryology data include total ova retrieved and total high-quality embryos. The high-quality embryos will be graded according to the guidelines (26, 27) by embryologists. Cleavage-stage embryos and blastocyst-stage embryos will be recorded separately.

The follow-up of pregnancy outcomes will be observed around 14 days and 12 weeks after embryo transfer. Besides CPR, the biochemical pregnancy rate (BPR), embryo implantation rate, and early miscarriage rate will also be observed, respectively. BPR is defined as the level of human chorionic gonadotropin (hCG) >5 mIU/mL (28). The fertilization rate is defined as the number of 2PN embryos divided by the number of inseminated oocytes. The early miscarriage rate is defined as the fetal growth stops or the absence of heart activity in the gestational sac within the first 12 weeks of pregnancy.

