**Methods and analysis:**

This clinical trial is a parallel, randomized, sham-controlled study. It aims to include a total of 118 infertile women who intend to undergo IVF. The participants will be randomly divided into three groups in a 1:1:1 ratio: the EA + IVF group, the placebo electro-acupuncture (pEA) +IVF group, and the IVF control group. All of the patients will be required to use ovarian stimulation drugs, while those in the EA + IVF and pEA + IVF groups will receive acupuncture treatment at three sessions per week (every other day) until trigger day with a minimum five session. The primary outcome of this trial will focus on the clinical pregnancy rate (CPR). CPR is defined as the rate of achieving clinical pregnancy from the first fresh/frozen embryo transfer cycle with an ultrasound-confirmed gestational sac in the uterine cavity. The secondary outcomes will assess embryology data, biochemical pregnancy rate, early miscarriage rate, Self-rating Anxiety Scale (SAS), Self-rating Depression Scale (SDS), Pittsburgh Sleep Quality Index (PSQI), Fertile Quality of Life (FertiQoL), patient retention rate, treatment adherence, and safety outcomes.

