Therefore, we have proposed to conduct a prospective, parallel, randomized, placebo-controlled trial that will be carried out to investigate the efficacy and safety of acupuncture treatment for patients with infertility, comparing them with placebo electro-acupuncture and IVF control groups. The current pilot study aims to assess the feasibility of performing a large-scale RCT, including patient recruitment, retention, and treatment adherence.

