### Intervention

Patients in the three groups will receive GnRH-a or GnRH-A protocol according to the previous study (21, 22). Egg retrieval, fertilization, and embryo transfer were determined by their fertility specialists. During the study period, the patients’ medications, including dose and types, should be recorded in detail.

Following the randomization, the patients who were randomized into the EA + IVF group and the pEA + IVF group will receive EA treatment during the ovarian stimulation phase at three times per week (every other day) until trigger day with a minimum five session. Each session will continue for 30 min. Licensed acupuncturists possessing a minimum of 1 to 3 years of clinical experience will undergo training in a standardized operating procedure. This training aims to impart a comprehensive understanding of the precise locations of acupoints and non-acupoints. Additionally, they will acquire proficiency in needle manipulation and the operation of electro-devices. Only acupuncturists who have completed this training will be authorized to perform acupuncture treatments.

The disposable needles (Hwato, Suzhou, Jiangsu, China) and the SDZ-V EA apparatus (Suzhou Medical Appliance) have the same appearance. The needle device used for blinding is comprised of a sticky plastic plate with a guide tube. The needles and blunt-tip needles will be administered through the guide tube and the hole of the plastic plate.

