### Outcome measurement

The assessors will record the baseline characteristics, including the couple’s age, ethnicity, body mass index (BMI), diagnosis of infertility, infertility history, previous IVF cycles, the level of AMH, AFC, the level of FSH, and LH. Ovarian response parameters (duration of stimulation, total dose of gonadotrophins, peak E2 level, and number of oocytes retrieved) will be used to assess the ovarian function during the ovarian stimulation (**Table 4**). The duration of stimulation is calculated from the first day of administrating gonadotropin to the hCG trigger. After the treatment, the participants will be questioned about the group allocation that they received.

**Table 4 T4:** Diagnosis definitions and time frame of outcomes.

Diagnosis	Definition	Time frame
Primary outcomes		
Clinical pregnancy^a^	Ultrasound-confirmed gestational sac	28 days after embryo transfer
Secondary outcomes		
Recruitment process		
Patient retention rate	The percentage of patients enrolled at baseline, who completed all follow-up measurements	Study completed
Adherence to treatment	Attendance at the treatment sessions	Study completed
Data on ovary induction		
Total dose of gonadotrophins (IU)	Was measured as the total dosage of gonadotropin drugs during the ovarian stimulation phase	On trigger day
Endometrium thickness (cm)	Was measured in the midsagittal plane of the thickness of the bilateral endometrium	On trigger day
Estrogen level pg/mL	Level of estrogen in the peripheral blood	On trigger day
Embryo data		
Ovum retrieved	Number of eggs retrieved from bilateral ovaries	On trigger day
High-quality embryos	Number of high quality measured by embryologists	3 or 5 days after the ovum was retrieved
Pregnancy outcomes		
Biochemical pregnancy^a^	Serum human chorionic gonadotropin ≥10 mIU/mL	10–14 days after embryo transfer
Early miscarriage^a^	Fetal growth stops or the absence of heart activity in the gestational sac within the first 12 weeks of pregnancy	Before 12 weeks in gestational age
Score of the questionnaires		
SAS	SAS consists of 20 items, and its measurement is determined by calculating the sum of the scores of each item	Baseline and on trigger day
SDS	SDS consists of 20 items, and its measurement is determined by calculating the sum of the scores of each item	Baseline and on trigger day
FertiQoL	FertiQoL contains 36 items, and its measurement is determined by calculating the sum of the scores of each item	Baseline and on trigger day

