This trial meets the methodological demand for adequate randomization, allocation concealment, and blinding of patients, outcome assessors, and statisticians. In this study design, there are several factors different from previous studies. Firstly, three treatment sessions per week during the ovarian stimulation and at least five sessions will be considerable. Previous studies conducted two before embryo transfer (8, 35), or one session was added on the 6–8 days of ovarian stimulation (three sessions in total) (9, 36). In these trials, the dose of acupuncture was far from adequate. In our previous meta-research, a high dosage of treatment showed better results for pregnancy outcomes. As a CAM, EA aims to improve the quality of the oocyte; enough dosage acupuncture will be needed as Magarelli (16) and White (37) have suggested. Secondly, EA with 2/100 Hz will be administered during the ovarian stimulation. In 1996, Stener-Victorin (38) found that EA can reduce the blood flow impedance in the uterine arteries. It is suggested that both of these effects are due to a central inhibition of the sympathetic activity. Moreover, Stener-Victorin reported that EA inhibits hyperactivity in the sympathetic nervous system in influencing ovarian morphology (39). For the tensity of electro-acupuncture, low tensity with 2–50 Hz was utilized frequently, especially in TEAS. However, low density and high tensity alternately will be more beneficial for long-duration treatment. Thus, this study is designed using EA with 2/100 Hz. Thirdly, acupoints were summarized from bibliographic retrieval. In total, 87 studies of acupuncture in treating infertility were screened and subjected to quality assessment. We ranked the acupoints with a high frequency utilized. CV12 (*Zhongwan*), ST25 (*Tianshu*), CV 6 (*Qihai*), CV4 (*Guanyuan*), KI12(*Dahe*), EX-CA1 (*Zigong*), SP10 (*Xuehai*), ST36 (*Zusanli*), SP6 (*Sanyinjiao*), LR3 (*Taichong*), BL23 (*Shenshu*), BL32 (*Ciliao*), and KI3 (*Taixi*) were recommended by 34 professors from all over the world. To our knowledge, CV 6 (*Qihai*), CV4 (*Guanyuan*), KI12 (*Dahe*), and EX-CA1 (*Zigong*) are positioned around nerves, which are connected with the ovaries and uterus (40). Blood vessels will be stimulated by nerve control. Moreover, the ovarian and uterus functions are governed by the hypothalamic–pituitary–ovarian (H–P–O) axis. Relaxing the depression and anxiety and improving the quality of life and sleep, the H–P–O axis might be influenced by stimulation. However, the placebo effect of EA cannot be ignored. We set a pEA in our pilot research; non-penetration of skin and blunt needles will be utilized to minimize the effect. To blind the patients successfully, we treated them separately and avoided communications.

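### The pilot's adherence target of four sessions is one below the regimen's own minimum of five, without explanation, and has no group-level pass mark

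*Protocol article*

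**What the plan says.** The Introduction of the protocol article names the feasibility questions that the pilot is meant to answer, "including patient recruitment, retention, and treatment adherence". The Secondary outcomes section turns these into three success targets: 114 participants recruited over 4 months, 80% retention, and "at least four treatment sessions attended".

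The dose is stated in three other places:

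- Abstract, Methods and analysis: "three sessions per week (every other day) until trigger day with a minimum five session".
- Intervention: "three times per week (every other day) until trigger day with a minimum five session".
- Discussion: "three treatment sessions per week during the ovarian stimulation and at least five sessions will be considerable". This is given as the first difference from earlier trials, of which the article says "In these trials, the dose of acupuncture was far from adequate".

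Table 4 defines retention as "The percentage of patients enrolled at baseline, who completed all follow-up measurements" but adherence only as "Attendance at the treatment sessions". The Statistical analysis section says that both will be summarised descriptively.

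**The concern.** Adherence is one of three named feasibility aims, and the pilot exists to support a definitive trial. A central question for that trial is whether at least five sessions can be delivered before trigger. A target of four does not test this, because a woman can satisfy it without receiving the minimum dose.

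The target also gives a session count without saying to whom it applies. It could mean every treated woman, the average woman, women who completed, or some share of women. If the choice is made once attendance is known, the target is no longer prespecified. Those planning the larger trial could then read a met target as evidence that the regimen is deliverable when it shows something weaker.

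**Working it through.** **Women concerned.** The Sample size section takes 30 per group and a 20% dropout rate: 30 / (1 − 0.20) = 37.5, rounded up to 38, and 3 × 38 = 114. This reproduces the article's figure. The IVF control arm has no sessions, so the target concerns 2 × 38 = 76 women.

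**Target against minimum.** 4 / 5 = 80%, a shortfall of one session. The article gives no derivation of the four, so there is no stated calculation to reproduce.

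**What the wording permits.**

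- All 76 women attend exactly four sessions: the target is met whether read per woman, as a mean or as a share, and 0 of 76 received the minimum.
- Read as a mean, with at most five sessions each: if 38 women attend three and 38 attend five, the mean is (3 + 5) / 2 = 4. The target is met while half the women are below four.

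**How far four and five can diverge.** The documents give no attendance data, so this is an illustration only. Assume five planned sessions, each attended independently with probability p. Then P(at least 4) = 5p⁴(1 − p) + p⁵ and P(all 5) = p⁵.

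| p | Reach four | Reach five | Gap (percentage points) |
|---|---|---|---|
| 0.80 | 73.7% (about 56 of 76) | 32.8% (about 25) | 41 |
| 0.90 | 91.9% (about 70) | 59.0% (about 45) | 33 |
| 0.95 | 97.7% (about 74) | 77.4% (about 59) | 20 |

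**Could early trigger explain four?** Count days from the first session to the last.

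- Strictly every other day, k sessions span 1 + 2(k − 1) days: 7 days for four, 9 for five.
- On a fixed Monday, Wednesday and Friday pattern, four sessions span 8 days from any start; five span 10 or 11.

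So there is a window of about 2 to 3 days in which a woman can complete four sessions but not five before trigger. How many women fall in it cannot be computed, because the article gives no distribution of stimulation length.

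**The case against.** The strongest reply is that the regimen and the feasibility threshold are different things, and a threshold may reasonably sit below the full course. Treatment stops at trigger, so a woman triggered early may attend every session offered and still not reach five. Four of five is also 80%, the same figure as the retention target. All of this is plausible. A reader might infer that four against five is an outright contradiction; the documents do not support that, since four may be a deliberate tolerance. What stands is that the article never says so, and an unexplained tolerance does not separate early trigger from missed sessions.

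A second reply is that adherence will be reported descriptively. A reader might infer that under-dosing would be hidden behind a bare pass or fail, but nothing in the article proposes such reporting, and the session counts may well be shown. This limits the harm. It does not repair the criterion, because descriptive figures do not settle whether a target with no pass mark was met.

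A third reply is that a journal article condenses a fuller protocol, where the denominator and share may be set. That is fair for detail left out. Here, though, the article itself defines the success targets and fixes this one at four, so the point concerns what is stated. If a pass mark exists elsewhere, it only needs to be carried over.

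Finally, a criterion of five alone would penalise women triggered early. That is correct, and the fix provides for it.

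**Conclusion.** The point holds as a minor correction to a feasibility criterion. The adherence target is one session below the intervention's stated minimum without a reason, and it lacks the group-level pass mark that the other two targets have. It can be declared met with anything from none to all of the 76 women receiving the minimum dose. The actual number affected cannot be derived from the documents, and the attendance probabilities above are assumptions.

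A reader might infer that the efficacy results are compromised. They are not: the intention-to-treat comparison of clinical pregnancy does not use this target, and the sample size of 114 reproduces. Nor do the documents show an effect on the per-protocol analysis, because completion of acupuncture is not tied there to four or five sessions.

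**What to change.** Restate the target as a prespecified proportion of the women randomised to EA and pEA who attend at least five sessions, reported by arm with a 95% CI. The pass mark is the sponsor's choice. As an example only, 80% would need 61 of 76 women overall (0.80 × 76 = 60.8; Wilson 95% CI 70.0% to 87.7%) or 31 of 38 in one arm (0.80 × 38 = 30.4; 66.6% to 90.8%).

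Show separately the women triggered before a fifth session was possible, so that early trigger is not counted as non-attendance.

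If four is a deliberate tolerance, keep it, state the reason, attach a proportion to it, and also report the share reaching five.

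The cost is a change to the wording of one target. Session attendance is already an outcome, so no new adherence measure is needed. The downside is that the adherence figure may look less favourable.

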#### Scale and questionnaire measurement

Anxiety and depression are the most prevalent mental illnesses contributing to the global infertility burden, which are also potential risk factors for IVF success. Emotional disorder can also lead to sleep problems and will influence the quality of life. Therefore, the scale and questionnaire measurement will be measured at baseline and on the trigger day to learn about changes in the mental disorder after the acupuncture treatments (**Table 4**). Self-rating anxiety scale (SAS) (29) and the self-rating depression scale (SDS) (30) are 20-item Likert scales, with raw scores that range from 20 to 80, which are converted to index scores by dividing the sum of the raw scores by 80 and multiplying by 100. Higher scores indicate greater severity of anxiety or depression symptomology. Index scores, 25–49 (raw scores 20–40); normal, 50–59 (raw scores 41–47); mild to moderate, 60–69 (raw scores 48–55); moderate to severe; and 70 and over (raw scores 56 and over), severe (31). The Pittsburgh Sleep Quality Index (PSQI) is a self-rated questionnaire to assess sleep quality and disturbance that can be used in clinical practice and research studies for patients with psychiatric or sleep problems and even among the general population (32). It contains 19 items in seven subdomains, including subjective sleep quality, sleep latency, sleep duration, habitual sleep efficiency sleep disturbances, use of sleeping medication, and daytime dysfunction (32). The sum scores of each item range daytime dysfunction from 0 to 21. The higher the patients’ scores, the worse sleep quality they experience. The fertile quality of life (FertiQoL) is an instrument to measure the quality of life in men and women experiencing fertility problems (33). FertiQoL consists of 36 items that assess core (24 items) treatment-related quality of life (QoL) (10 items) and overall life and physical health (two items). The items in the prototype FertiQoL survey were randomly presented and rated on a scale of 0–4, where higher scores indicated a more favorable quality of life.

#### Blinding assessment

To test whether blinding is successful, patients in the EA + IVF group and pEA + IVF group will be asked to guess which kind of acupuncture they received at hCG trigger day after finishing the acupuncture treatment.

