**Figure 1 f1:**
[figure not shown]
Flow diagram. IVF, *in vitro* fertilization; EA, electro-acupuncture.

**Table 1 T1:** Schedule of recruitment, intervention, and measures.

Items	Enrolment	Intervention	Follow-up			
	Screening and baseline assessment	Controlled ovarian hyperstimulation	Oocyte retrieval	Embryo transfer	14 days after embryo transfer	28 days after embryo transfer
Enrolment						
Eligibility screen	×					
Informed consent	×					
Allocation	×					
Baseline data	×					
Randomization						
Randomization	×					
Allocation	×					
Interventions						
EA/ pEA treatment		×				
COH treatment		×				
Assessments						
Laboratory tests	×	×	×	×	×	×
Embryo quality				×		
Pregnancy tests					×	×
Pregnancy outcomes				×	×	×
Fetus information						
FertiQoL	×		×			
SAS	×		×			
SDS	×		×			
PSQI	×		×			
Blinding assessments			×			
Adverse events		×	×	×	×	×
Retention rate						×
Adherence to treatment						×

EA, electro-acupuncture; pEA, placebo electro-acupuncture; COH, controlled ovarian hyperstimulation; FertiQoL, fertile quality of life; SAS, self-rating anxiety scale; SDS, self-rating depression scale. PSQI, Pittsburgh Sleep Quality Index.

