### Statistical analysis

Intention-to-treat (ITT) analysis encompassing all randomized patients will be conducted for all efficacy analyses. Additionally, a per-protocol (PP) analysis focusing on the primary outcome will be performed as a sensitive analysis, excluding patients who did not complete the acupuncture treatment. Missing outcome data will be complemented using multiple imputations with the package “Mice” from the R software (www.r-project.org).

Categorical variables will be reported by number and percentage, whereas continuous variables will be represented by mean and standard deviation (SD) (or median and interquartile range, IQR). The retention rate and treatment adherence will be reported in descriptive statistics.

For the primary outcome, CPR will be compared by the proportions of included patients with clinical pregnancy. To determine the independent factors, logistic regression will be used to identify baseline variables that are associated with outcomes. The retention rate and rates of biochemical pregnancy, ongoing pregnancy, blinding assessments, and adverse events will undergo statistical analysis using chi-squared tests or Fisher’s exact test. Other outcomes will be evaluated using one-way variance (ANOVA) models or Kruskal–Wallis analysis. The score of SAS, SDS, FertiQol, and PSQI, respectively, will be assessed at baseline and after treatment among groups on hCG trigger day. Statistical significance will be determined at *P <*0.05. Pairwise comparisons will be performed between the EA + IVF group and the pEA + IVF group and between the EA + IVF group and the IVF group in a *post hoc* analysis.

A predetermined subgroup analysis will be performed to determine whether the baseline characteristics (female age, ovarian stimulation protocol, etc.) affect the CPR to EA. The data was analyzed using SPSS version 27.0 (IBM, Armonk, NY, USA). As this is a pilot study, our results were considered exploratory.

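### The blinding guess is scheduled only at hCG trigger day after acupuncture is finished, so women cancelled before trigger, and on a literal reading those who stop needling early, are not asked

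*Protocol article*

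**What the plan says.** The article times the blinding guess in three places, and they do not agree.

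- Blinding assessment: women in the EA + IVF and pEA + IVF arms "will be asked to guess which kind of acupuncture they received at hCG trigger day after finishing the acupuncture treatment". This gives a day and a condition.
- Outcome measurement, opening paragraph: "After the treatment, the participants will be questioned about the group allocation that they received". This gives neither a day nor a completion condition.
- Table 1: the row "Blinding assessments" is marked under oocyte retrieval. The table has no trigger-day column and no early-stop contact.

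The four questionnaires (SAS, SDS, PSQI, FertiQoL) have a baseline and one later measurement. The section on scales says "the scale and questionnaire measurement will be measured at baseline and on the trigger day", and Table 4 gives "Baseline and on trigger day" for each. Table 1 again marks the later measurement under oocyte retrieval.

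On analysis, the Statistical analysis section states "Intention-to-treat (ITT) analysis encompassing all randomized patients will be conducted for all efficacy analyses" and "Missing outcome data will be complemented using multiple imputations with the package “Mice” from the R software". It sends the blinding assessments to a chi-squared or Fisher's exact test. The exclusion of women who did not complete acupuncture applies only to the per-protocol analysis of the primary outcome.

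**The concern.** The guess is there to show whether the placebo was credible. That evidence matters here because the pilot is meant to support a definitive sham-controlled trial and the Discussion claims that patients are blinded. The two procedures can be told apart in principle. EA penetrates the skin, seeks De qi and uses a current of 0.1 to 5 mA set to comfort. pEA does not penetrate, avoids De qi and uses 0.1 mA.

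Women who recognise the placebo may be among those who leave it. If so, a question put only to women who finish misses the women who are most informative about credibility, and the placebo looks more convincing than it was. The designers of the definitive trial would then carry forward a sham procedure on evidence that is too favourable. No later analysis plan can recover a guess that was never collected.

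**Working it through.** **The plan's own figures.** The Sample size section takes 30 women per group and 20% drop-out. 30 / (1 − 0.20) = 37.5, rounded up to 38 per group, and 3 × 38 = 114. The stated 114 reproduces. The two acupuncture arms together hold 2 × 38 = 76 women. (The abstract and the limitations paragraph give 118 instead; this does not bear on the point.)

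**Who is asked.** The wording of the Blinding assessment section gives four cases:

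1. Needling finished, trigger reached: asked.
2. Stimulation cancelled before trigger: there is no trigger day, so no guess is scheduled.
3. Needling stopped early, stimulation continues to trigger: on a literal reading not asked, because treatment was not finished. On a looser reading (needling is over) she is asked.
4. Fewer sessions than planned: unclear. The Intervention section sets a minimum of five sessions, whereas the pilot target under Secondary outcomes counts at least four as success. The article does not say which, if either, defines having finished.

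If Table 1 governs instead, the guess comes later still, and a woman without a retrieval is missed as well.

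**How many.** The article gives no cancellation or needling-stop rate. The number of guesses expected from 76 women at an assumed missing share m is 76 × (1 − m):

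- m = 5%: 72.2, about 72
- m = 10%: 68.4, about 68
- m = 20%: 60.8, about 61

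The 20% is the article's overall drop-out allowance. It includes losses after trigger, which do not affect the guess, so it is an upper bound: 0.20 × 38 = 7.6 women per acupuncture arm at most.

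**How far the result could move.** Let completers guess correctly with probability 0.50 and women not asked with probability q (both assumed). The rate among all treated women is (1 − m) × 0.50 + m × q, while the reported rate is 0.50.

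| m | q = 70% | q = 90% | q = 100% |
|---|---|---|---|
| 5% | 51% | 52% | 52.5% |
| 10% | 52% | 54% | 55% |
| 20% | 54% | 58% | 60% |

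For example, with m = 20% and q = 90%: 0.80 × 0.50 + 0.20 × 0.90 = 0.40 + 0.18 = 0.58.

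**Whether the planned analysis repairs it.** The intention-to-treat sentence covers efficacy analyses, and a blinding guess is not clearly one of these. Even if the guess were counted as outcome data and imputed, women of the kind who are never asked would supply no observed guess for the imputation model to learn from.

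**The questionnaires.** Nothing makes them conditional on finishing acupuncture. A woman in case 3 is due all four at trigger day. Only case 2 leaves a woman with a baseline score and no scheduled later one.

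**The case against.** The wording may only fix the order of events: ask once needling is over. The statement in the Outcome measurement section carries no completion condition, which supports that reading. This stands to the extent that the exclusion of early needling stoppers is a literal reading, not an explicit rule. It does not help women cancelled before trigger, who have no trigger day on either reading.

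An early-termination contact is often described in a full protocol that is not shown. However, the article does not merely omit the detail. It states a time point and a condition, and states them differently elsewhere.

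The shift is also small relative to the precision of the pilot. The standard error of a 50% proportion in 38 women is sqrt(0.25 / 38) = 8.1 percentage points, so even the 8-point gap in the example (58% against 50%) is about one standard error. At 5% missing the gap is 1 to 2.5 points for q from 70% to 100%. Results are declared exploratory. All of this stands and keeps the point modest.

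A reader might go further and infer that women who stop needling also lose the questionnaires, so that both sets of results describe completers. The documents do not support that. The questionnaires have a baseline measurement and do not depend on finishing acupuncture, and all randomised women are to be analysed with multiple imputation. The imputation may be imperfect for cancelled cycles, because none of them would have an observed later score, but that is not a completer analysis.

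**Conclusion.** The point holds for the blinding guess. As scheduled, it misses women in EA and pEA whose stimulation is cancelled before trigger and, read literally, those who stop needling early. The result risks describing completers.

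Under the assumed 50% and 90% guess rates, the understatement is 2 points at 5% missing, 4 points at 10% and 8 points at the 20% upper bound. The direction rests on the assumption that women not asked guess correctly more often than completers. If they guess at the same rate there is no bias, and if they guess correctly less often, blinding would look worse than it was.

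For the questionnaires, what holds is limited to the missing post-baseline score in women cancelled before trigger, and to the conflict between Table 1 (oocyte retrieval) and the text and Table 4 (trigger day). This is a cheap improvement to a stated time point, not a flaw that undermines the trial.

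**What to change.** In the Blinding assessment section, set the guess in EA and pEA at trigger day or, if earlier, the day on which acupuncture is stopped or the cycle is cancelled, collected in person or by phone. Report it overall and separately for women who completed acupuncture and those who did not, and say what counts as completion. Bring Table 1, the Outcome measurement paragraph and the Blinding assessment section to one time point.

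For the questionnaires, reconcile Table 1 with Table 4 and the section on scales, and state that women cancelled before trigger have no scheduled later score. Adding a questionnaire at cancellation is more debatable, because it would also capture the reaction to the cancellation, and it is not needed to resolve this point.

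The cost is one extra use of an existing form for a few women, whose guess is taken on a slightly different day from the others.
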